### Patient and public involvement

Patients or the public will not be involved in the design or conduct of the study. Results will be disseminated to the community.

### Study status

Recruitment began in August 2019 and field activities and data collection are in process. As of 16 October 2020, a total of 235 cases and 184 controls have been enrolled. Extension of study duration is in discussion to achieve sample size.

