**Figure 2 F2:**
[figure not shown]
Map of intervention and control sites Abbreviations used in Map: Liaqat University of Medical and Health Sciences Jamshoro (LUMHS). Legend: Lady Health Worker (LHW). Service Layer Credits: Companies/institutes which contributed and collaborated to make this basemap publicly available (Environmental Systems Research Institute (ESRI), HERE (private company), General Bathymetric Chart of the Oceans (GEBCO), US Geological Survey (USGS), Food and Agriculture (FAO), National Park Service (NPS), National Resources Canada (NRCan), GeoBase, Institut Geographique National (IGN), Ministry of Economy, Trade and Industry (METI).

Participants will be the permanent residents of Kotri, Jamshoro and recruited from their homes during routine monthly visits by LHWs serving in their catchment areas. This study is expected to run for 48 months with participant identification and enrolment conducted simultaneously in intervention and control clusters over 21 months after an initial pilot of 1 month. Each enrolled child will be revisited at day 7 and 14 for outcome measurement.

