### Randomisation and masking

Study clusters were defined as the area covered by an LHW. Each LHW covers a minimum of 100 households. A list of LHWs working in Kotri was collected from the LHW programme, health department government of Sindh. There are a total of 188 active LHWs in the study site. A baseline survey was conducted to collect data on health indicators from the LHW catchments. The clusters were randomly allocated to intervention and control groups on 1:1 fashion with a computer-generated randomisation sequence that was generated by an independent expert. Clusters were matched on under 5 population and distance to referral health facility. No stratification was used for allocation; clusters were selected to ensure that the reporting and training centres of intervention and control LHWs were separate. The investigators and the national and provincial LHW programme coordinators will be excluded from the allocation process.

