### Sample size

Defining a cluster as (the catchment area of) one LHW, and assuming a power of 90% in detecting 50% increase in referral acceptance from a 10% baseline to 15% among children aged 0–59 months with severe pneumonia (pneumonia prevalence at 2-week recall (MICS Sindh): 7.5% (18% of which is assumed severe pneumonia) with ICC 0.001736. We need to capture a total of 4160 children with severe pneumonia in both intervention and control groups.

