### Data analysis

The primary analysis for each outcome will perform on an ‘intention-to-treat’ basis, that is, all children included in the analysis who were enrolled in the study according to the group to which they were allocated. All analyses will account for the cluster randomised design to ensure correct type I error rates and CIs.^35^ Baseline characteristics will be compared by analysing differences in means and proportions among the study arms. Categorical outcomes will be compared using χ^2^ test and continuous outcomes using Student’s t-test. For analysis of predictors of referral acceptance, generalised linear model will be used with logit link function. The univariate analysis will be conducted to explore the independent effect of each predictor on outcome. The variables significant at a liberal p<0.20 will be included in multivariate model for adjustment. The results will be reported as relative risk with 95% CI. Type 1 error will be set at 5% level. All analysis will be done using STATA V.15.

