### Limitations

Some union councils with poor LHW coverage were not included in this study. This was a compromise on generalisability in favour of feasibility. It may have led to exclusion of children whose referral patterns were important to gauge. We also did not offer facilitated referral in either arm. This may have affected referral acceptance in both groups, however, will allow assessment of real-life impact of transportation barriers.

Though we kept hospital referral (as recommended by WHO) for severe pneumonia as our standard of care, it was beyond the scope of this study to ensure that referral centres had sustainable oxygen systems/capacity for non-invasive ventilation in children with severe pneumonia, or readily available cardiac evaluation resources for children with hypoxaemia alone. Duke *et al* showed improved case fatality rates by providing oxygen concentrators and pulse oximeters at five hospitals in PNG along with protocols for use.^35^ Lack of quality care at referral hospitals in developing countries is a recognised barrier to healthcare seeking behaviour.^40 41^

If our study reveals pulse oximetry has influenced health-seeking behaviour significantly, we will need to follow with a more systematic evaluation of pneumonia care at rural hospitals which vary in quality of care. We will also need to correlate recovery rates in those who accepted hospital referral versus those who stayed home on oral amoxicillin. Evidence to support home care for severe pneumonia is poor.^42^

The COVID-19 pandemic has adversely affected recruitment in the study with disruption of field activities for many months in 2020. We anticipate prolongation of study duration in order to achieve sample size.

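### At the reported pace neither 4160 children nor 90% power is reached in 21 months, and the open-ended extension is tied to a total that the stated inputs do not require

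*Protocol article*

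**What the plan says.** The Sample size section states its aim as "assuming a power of 90% in detecting 50% increase in referral acceptance from a 10% baseline to 15" per cent, "with ICC 0.001736", and concludes: "We need to capture a total of 4160 children with severe pneumonia in both intervention and control groups". Data analysis adds "Type 1 error will be set at 5% level" without saying whether the test is one- or two-sided. Randomisation and masking says that clusters were "randomly allocated to intervention and control groups on 1:1 fashion" and that 188 lady health workers are active in the site. It does not say that all 188 catchments were randomised.

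Trial setting gives a 48-month study with "enrolment conducted simultaneously in intervention and control clusters over 21 months after an initial pilot of 1 month".

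Study status dates the start of recruitment to August 2019 and reports: "As of 16 October 2020, a total of 235 cases and 184 controls have been enrolled". It says that an extension is under discussion. Limitations attributes the delay to pandemic disruption lasting many months of 2020, with no number given, and adds: "We anticipate prolongation of study duration in order to achieve sample size". No extension length, revised rate, revised target or revised power is given.

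**The concern.** The plan needs 4160 / 21 = 198 children per month. The reported count works out at 29 to 31 per month. About two thirds of the enrolment window had passed with a tenth of the children enrolled.

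Two things are at stake. If enrolment closes near the written window, the power for the trial's own target effect is far below the 90% on record, and a non-significant result could be misread as evidence that oximetry does not raise acceptance. If instead enrolment runs on until 4160, the trial has no foreseeable end at this pace, although far fewer children would give the stated power.

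**Working it through.** **Inputs from the article:** acceptance 10% vs 15%, power 90%, ICC 0.001736 and total 4160 (Sample size); 5% type 1 error (Data analysis); 1:1 allocation (Randomisation and masking); 21 and 48 months (Trial setting); 235 + 184 = 419 enrolled from August 2019 to 16 October 2020 (Study status).

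**Assumptions:** two-sided test; 188 equal clusters; 0, 4 or 8 months wholly lost to the pandemic; recruitment starting between 1 August (14.5 months elapsed) and 31 August (13.5 months).

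**Step 1: the plan's own total.** Per arm, with mean proportion 0.125:

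n = [1.96·√(2·0.125·0.875) + 1.2816·√(0.10·0.90 + 0.15·0.85)]² / 0.05² = (0.9167 + 0.5977)² / 0.0025 ≈ 918, so 1836 in total (1914 with continuity correction).

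The design effect is DE = 1 + (N/188 − 1)·0.001736. Solving N = 1836·DE gives 1864 (DE 1.0155); the continuity-corrected version gives 1945. The stated 4160 is not reproduced. It would need DE = 4160/1836 = 2.27, that is 1 + 1.266/0.001736 ≈ 730 children per cluster in about 6 clusters (about 680 per cluster with continuity correction). At 4160 children in 188 clusters the power is about 99.8%.

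**Step 2: projection.** With L months lost and T months elapsed, rate r = 419/(T − L). Enrolment at 21 calendar months is 419 + r·(21 − T). If the lost months are added back so that 21 are fully active, it is 21·r. Total months to reach N are N/r + L.

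**Step 3: power at the projected N.** With n = N/(2·DE), power = Φ{[0.05·√n − 0.9167] / 0.4664}. For N = 607: DE = 1.0039, n = 302, and power = Φ(−0.10) = 46%.

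| Elapsed, lost (months) | Rate per month | N at 21 calendar months (power) | N at 21 active months (power) | Total months to 4160 | Total months to 1864–1945 |
|---|---|---|---|---|---|
| 14.5, 0 | 28.9 | 607 (46%) | 607 (46%) | 144 | 65–67 |
| 13.5, 0 | 31.0 | 652 (49%) | 652 (49%) | 134 | 60–63 |
| 14.5, 4 | 39.9 | 678 (50%) | 838 (59%) | 108 | 51–53 |
| 13.5, 4 | 44.1 | 750 (54%) | 926 (63%) | 98 | 46–48 |
| 14.5, 8 | 64.5 | 838 (59%) | 1354 (79%) | 73 | 37–38 |
| 13.5, 8 | 76.2 | 990 (66%) | 1600 (85%) | 63 | 32–34 |

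Using the observed 235:184 split instead of 1:1 changes little: 44.5% rather than 46% at 607. With about 607 children, 90% power exists only for a rise from 10% to about 19%.

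**Step 4: the 48-month frame.** Even if all 48 months were enrolment, the total would run from 48 × 28.9 ≈ 1390 to (48 − 8) × 76.2 ≈ 3050, short of 4160 in every scenario.

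**The case against.** The strongest reply is that the article does not claim 21 months will be enough. It reports the shortfall, names the pandemic and expects to run longer, so the low power figures describe a stopping point that the authors do not intend. That stands. The defect is not concealment. It is that the stated remedy has no length, and the total it aims at lies beyond the study's stated duration at any rate the reported count supports.

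The second reply also stands: missing 4160 is not the same as missing 90% power. A reader might infer that the trial cannot reach its stated power. The documents do not support this, because by the same formula about 1860–1950 children are enough. With 8 months lost that is about 32–38 months of enrolment in total, and with 4 lost about 46–53.

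A reader might also infer that no extension could ever reach 4160. That goes too far. The count includes a start-up period and a disrupted year, and nothing rules out a faster rate, although the article names no measure to achieve one.

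Nor can the prevalence inputs in the sample-size text be called refuted by the low yield. The article gives no under-5 share, does not confirm 188 randomised clusters, and does not present those inputs as a yield per visit round.

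Finally, the number of lost months is unknown, so the power figures are scenarios and not a forecast.

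**Conclusion.** The point holds in this form. On the two-sided calculation no scenario tried delivers 4160 children or 90% power within 21 months: about 610–990 children and 46–66% power on calendar months, and at most about 1350–1600 and 79–85% with 21 active months after 8 lost. Reaching 4160 takes about 63–144 months of enrolment against a 48-month study, unless the rate rises. The extension is therefore tied to a figure that is not reachable at this pace and not required by the stated inputs.

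The result rests on a two-sided test, 188 clusters of equal size and the assumed lost months. Sidedness matters only at the edge: a one-sided 5% test would need about 1514 children for 90% power, which only the most generous scenario (1600) exceeds. The gap to 4160 is unaffected. Because the ICC is small, the number of clusters has little influence on the projected power at these sample sizes unless it is very low.

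**What to change.** In Sample size, re-derive the target from the stated inputs, showing sidedness, number of clusters and children per cluster. If 4160 rests on an input not printed, print it.

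In Study status and Limitations, replace the open-ended extension with:

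- a stated end date for enrolment;
- the number of children that date delivers at the observed rate, both crude and with lost months excluded, with the lost months labelled as an assumption;
- the power for 10% vs 15% at that number, and the difference detectable with 90% power.

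The end date need not fall inside the 48 months. The article does not say when those months began, and such a cap could lock in low power when a longer extension to about 1900 children would restore it.

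The change is to text only and needs no extra patients or staff. Its cost is that the published figures become less favourable.

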## Discussion

Hypoxaemia, a frequent complication of severe pneumonia, is a major risk factor for death in children under 5. Theoretically, detection of hypoxaemia at community level among severe pneumonia cases by the use of pulse oximeter would give awareness to the caregivers about severity of illness and reduce delay in hospital referral. Delayed care-seeking is a recognised risk factor in pneumonia mortality in community settings.^36^ Unfortunately, information on prevalence of hypoxaemia, effectiveness of its detection in influencing parents to seek hospital care (gold standard for severe pneumonia) and impact of appropriate care at hospital in settings like Pakistan is lacking. Thus, the findings of this study will build evidence for utility of providing front-line workers like LHWs with a tool to detect hypoxaemia if signs and symptoms of pneumonia are present. Interestingly various groups across the world are now espousing pulse oximetry with other strengths like detection of congenital heart disease^37 38^ and newborn sepsis.^39^

### Limitations

Some union councils with poor LHW coverage were not included in this study. This was a compromise on generalisability in favour of feasibility. It may have led to exclusion of children whose referral patterns were important to gauge. We also did not offer facilitated referral in either arm. This may have affected referral acceptance in both groups, however, will allow assessment of real-life impact of transportation barriers.

Though we kept hospital referral (as recommended by WHO) for severe pneumonia as our standard of care, it was beyond the scope of this study to ensure that referral centres had sustainable oxygen systems/capacity for non-invasive ventilation in children with severe pneumonia, or readily available cardiac evaluation resources for children with hypoxaemia alone. Duke *et al* showed improved case fatality rates by providing oxygen concentrators and pulse oximeters at five hospitals in PNG along with protocols for use.^35^ Lack of quality care at referral hospitals in developing countries is a recognised barrier to healthcare seeking behaviour.^40 41^

If our study reveals pulse oximetry has influenced health-seeking behaviour significantly, we will need to follow with a more systematic evaluation of pneumonia care at rural hospitals which vary in quality of care. We will also need to correlate recovery rates in those who accepted hospital referral versus those who stayed home on oral amoxicillin. Evidence to support home care for severe pneumonia is poor.^42^

The COVID-19 pandemic has adversely affected recruitment in the study with disruption of field activities for many months in 2020. We anticipate prolongation of study duration in order to achieve sample size.

## Ethics and dissemination

This study has been approved by the Ethical Review Committee of The Aga Khan University (4722-Ped-ERC-17), Karachi, Pakistan in June 2017. Written informed consent in the local language will be obtained from parents or guardians of all participants. Data forms will contain no identifying information other than age, sex and GIS coordinates. Laboratory forms will contain no identifying information, specimens will be identified by a study number only and test results will not be linked to any individual by name. All survey staff will sign a confidentiality agreement to ensure that they do not release participant identities and test or study results to individuals who are not part of the study team.

Study progress and findings will be shared with sponsors (BMGF) quarterly. Results will be presented at national and international research meetings and conferences and also prepared for publication in international peer-reviewed scientific journals. Study findings will be disseminated to the study communities.
